## Abstract

In Japan, corticosteroid monotherapy has traditionally been recommended as the first-line therapy for membranous nephropathy with nephrotic syndrome. In contrast, except for Japan, rituximab is recommended as the first-line therapy for membranous nephropathy with nephrotic syndrome. This clinical trial aimed to verify the efficacy and safety of the intravenous administration of rituximab without steroids or immunosuppressants as an induction therapy in Japanese patients with idiopathic membranous nephropathy and nephrotic syndrome. This was a multicentre (15 in Japan), placebo-controlled, randomized, double-blind, parallel-group comparative study. A total of 88 patients diagnosed with idiopathic membranous nephropathy and nephrotic syndrome were randomly allocated to rituximab and placebo groups in a 1:1 ratio; rituximab 1,000 mg or placebo IV infusion was administered every 2 weeks for two doses in a double-blinded manner. The primary endpoint was the percentage of patients achieving less than 1.0 g/g creatinine in urine protein/creatinine ratio in random urine at 26 weeks after the first administration of rituximab or placebo. This study was approved by the institutional review boards and conducted in accordance with the Good Clinical Practice guidelines. This study was registered at ClinicalTrials.gov, NCT05914155 and the Japan Registry of Clinical Trials, jRCT2041230037 on 13 June 2023.

## Introduction

Nephrotic syndrome is characterized by massive urinary protein leakage associated with enhanced protein permeability due to glomerular loop disorders and hypoproteinemia (hypoalbuminemia) associated with the leakage. The main diagnostic criteria for adult nephrotic syndrome in Japan are as follows: 1) urine protein ≥3.5 g per day persists (urine protein/creatinine ratio ≥3.5 g/g creatinine in random urine will be handled similarly), and 2) hypoalbuminemia: serum albumin ≤3.0 g/dL (total serum protein ≤6.0 g/dL can be used as reference). Membranous nephropathy is one of the most frequent causative diseases of nephrotic syndrome developing in middle-aged or older individuals, and nephrotic syndrome due to membranous nephropathy is characterized by a relatively slow progression of urine protein and oedema. Approximately 70% of these patients develop nephrotic syndrome [1], and approximately 40% of them develop refractory nephrotic syndrome. Membranous nephropathy is characterized by the thickening of the glomerular basal membrane as a histopathological finding on renal biopsy. Since approximately 20–30% of the patients are spontaneously remitted in the observation of long-term prognosis, membranous nephropathy is said to be relatively benign in glomerular nephritis. However, cases resulting in nephrotic syndrome might have an unfavorable prognosis. A Japanese study has reported that the kidney survival rates of idiopathic membranous nephropathy with nephrotic syndrome are 90.3%, 81.1%, and 60.5% after 10, 15, and 20 years, respectively [2]. On the other hand, a Finnish study on the prognosis of adult patients with idiopathic membranous nephropathy, with urine protein ≥3.0 g per day, reported that 24% of the patients died or had dialysis introduced at year 10 (patient survival rate 80% and kidney survival rate 64%) [3]. Since a decrease in urine protein was reported to be related to an improvement in prognosis, it is considered important to achieve complete or incomplete remission as early as possible.

The 2021 Clinical Practice Guidelines for the Management of Glomerular Disease (KDIGO Guidelines) consider rituximab or calcineurin inhibitors, including cyclosporine and tacrolimus, as first-line drugs for patients with membranous nephropathy at moderate to high risk corresponding to nephrotic syndrome [4]. According to the Japanese guidelines, oral steroid monotherapy is recommended as one of the first-line therapies [5]; however, the KDIGO guidelines do not recommend a single steroid. The Japanese clinical guidelines permit the start of treatment with any of the following: (1) supportive therapy (non-immunosuppressive therapy including diuretics, angiotensin-converting enzyme inhibitors, angiotensin receptor blockers, and antiplatelet drugs); conservative therapies for lifestyle education (smoking cessation and body weight control), salt restriction, and diet; (2) steroid monotherapy; or (3) a combination therapy with steroids and immunosuppressants in addition to (1) supportive therapy. In Japanese epidemiological research, patients using corticosteroids have a high incidence of infection, which is a critical issue in membranous nephropathy [6].

A randomized open-label control study to compare the efficacy of rituximab and conservative therapy (GEMRITUX study) [7] and a randomized open-label non-inferiority study to compare the efficacy of rituximab and cyclosporine (MENTOR study) [8,9] were performed, and rituximab was found to be effective and safe. However, rituximab is not permitted for use in treatment under the Japanese National Health Insurance. Therefore, a prospective placebo-controlled double-blind parallel group study has been planned to examine the therapeutic effect of rituximab in Japanese patients with idiopathic membranous nephropathy with nephrotic syndrome as an investigator-initiated clinical trial. This clinical trial has been named “The multi-center, randomized, double-blind, placebo-controlled study to evaluate the efficacy and safety of rituximab (genetical recombination) for the treatment for idiopathic membranous nephropathy with nephrotic syndrome” (PRIME trial). We discussed the design of this investigator-initiated clinical trial, aimed at evaluating the efficacy and safety of this therapy, in a consultation meeting with the Pharmaceuticals and Medical Device Agency (PMDA), which is the regulatory authority for new drugs in Japan, and the PMDA accepted our proposal.

## Materials and Methods

### Objective, overall design, and framework

The primary objective of this clinical study was to confirm the efficacy and safety of intravenous rituximab in patients diagnosed with idiopathic membranous nephropathy with nephrotic syndrome. The primary endpoint was the percentage of patients achieving incomplete remission type I (ICR I) with the urine protein/creatinine ratio <  1.0 g/g creatinine. The criteria for treatment effects are shown in Table 1.

**Table 1 pone.0320070.t001:** Criteria for treatment effects.

CR	Urine protein/creatinine ratio < 0.3 g/g creatinine
ICR I	0.3 g/g creatinine ≤ Urine protein/creatinine ratio < 1.0 g/g creatinine
ICR II	1.0 g/g creatinine ≤ Urine protein/creatinine ratio < 3.5 g/g creatinine
NR	Urine protein/creatinine ratio ≥ 3.5 g/g creatinine
PR	Decrease in urine protein/creatinine ratio from base line ≥ 50%, and urine protein-creatinine ratio 0.3 to 3.5 g/g creatinine

The treatment effect will be evaluated using random urine samples at each point after the administration of the investigational drugs.

CR: Complete Remission, ICR I: Incomplete Remission Type I, ICR II: Incomplete Remission Type II, NR: No Response, PR: Partial Response

The PRIME study is a placebo-controlled, randomized, double-blind, parallel-group, comparative study, followed by an open-label, single-arm study. In the double-blind phase of this trial, patients will be randomly allocated to rituximab and placebo groups in a 1:1 ratio, and rituximab 1,000 mg or placebo infusion will be administered every 2 weeks for two doses in a double-blinded manner. However, if patients with incomplete remission type II (ICR II) or no response (NR) until the evaluation at week 26 in the double-blind phase wish to move to the open-label phase, and the investigator considers the move necessary, the patient may move to the open-label phase and receive intravenous infusion of rituximab 1,000 mg every 2 weeks for two doses. This move will be performed after the eligibility criteria for re-administration is confirmed. An outline of this clinical trial is shown in Fig 1.

**Fig 1 pone.0320070.g001:**
[figure not shown]
Flowchart of this trial. This shows the schema of this trial, timing of administration of investigational drugs (rituximab or placebo), and assessments and visits for each patient in each phase.

### Eligibility criteria

We will recruit a maximum of 88 patients with nephrotic syndrome due to membranous nephropathy in a double-blind phase. The inclusion and exclusion criteria are follows.

#### Inclusion criteria.

1) Patients who underwent kidney biopsy and are diagnosed as having idiopathic membranous nephropathy prior to obtaining informed consent (i).2) Patients diagnosed as having nephrotic syndrome prior to obtaining informed consent (i) and who received no steroids or immunosuppressants within 12 weeks prior to obtaining informed consent.3) Patients with urine protein/creatinine ratio ≥3.5 g/g creatinine at screening (i).4) Patients with hypoalbuminemia (serum albumin ≤3.0 g/dL) at screening (i).5) Patients aged 15 years or older at informed consent (i).6) Patients who provide voluntary written consent after receiving adequate information about this study (legally acceptable representatives should also give consent to patients under 18 years old, and informed assent should be obtained from children).

#### Exclusion criteria.

1) Primary nephrotic syndrome other than membranous nephropathy (IgA nephropathy, minimal change disease, focal segmental glomerulosclerosis, etc.) and secondary nephrotic syndrome (autoimmune disease, metabolic disease, infection, allergic/hypersensitive disease, tumour, and drug-induced disease).2) Lower renal function (estimated glomerular filtration rate (eGFR) < 30 mL/min/1.73 m^2^ based on the Chronic Kidney Disease Epidemiology Collaboration (CKD-EPI) equations) at screening (i).3) Patients who have used anti-CD20 antibody, including rituximab, for idiopathic membranous nephropathy.4) Participation in another clinical study within 12 weeks prior to obtaining informed consent (i) or participation in another study.5) Patients with a history of renal transplant.6) Patients with poorly controlled diabetes (HbA1c value of 8.0 or higher).7) Patients who have or are suspected of having an active infection at the time of informed consent (i).8) Patients who test positive for HBs antigen, and HBs, HBc, and/or HCV antibodies (patients with positive HBs antibody and/or HBc antibody can be enrolled only when HBV-DNA test is negative by taking appropriate measures, such as periodic monitoring of HBV-DNA and AST/ALT; patients with positive HCV antibody can be enrolled only when HCV-RNA test is negative), or patients with positive HIV or HTLV-1 antibody at the time of screening (i).9) Patients with leukopenia (less than 2,000/mm^3^), neutropenia (less than 1,000/mm^3^), or lymphopenia (less than 500/mm^3^) at screening (i).10) Patients with a history of serious hypersensitivity or anaphylactic reaction to one of the ingredients in the investigational drug or murine protein-containing products.11) Patients who are judged to be having life-threatening nephrotic syndrome by the investigator or sub-investigator.12) Serious comorbidities (e.g., hepatic, renal (excluding idiopathic membranous nephropathy with nephrotic syndrome), cardiac, lung, haematologic, or brain disease).13) Female patients who are pregnant, lactating, or potentially pregnant, or patients who are not willing to use contraceptive measures during the study period.14) Patients who are judged to be unsuitable by the investigator or a sub-investigator

#### Eligibility criteria for re-administration.

The inclusion criteria for open-label phase are as follows.

1)Patients who received the investigational drug in the double-blind phase and showed ICR II or NR until the time of evaluation at week 26, met the following criteria, and wished to have a re-challenge with rituximab.2)Patients who received no corticosteroids or immunosuppressants between the obtainment of informed consents (i) and (ii).3)Patients who gave their voluntary written consent after receiving adequate information about the open-label phase of this study (legally acceptable representatives should also give consent to patients under 18 years old, and informed assent should be obtained from children).

#### Exclusion criteria for re-administration.

1)Patients with renal function lowered (eGFR < 30 mL/min/1.73 m^2^ based on CKD-EPI equations) at screening (ii).2)Participation in another clinical study within 12 weeks prior to providing informed consent (ii) or participation in another study.3)Patients with a history of renal transplant prior to the obtainment of informed consent (ii).4)Patients with poorly controlled diabetes (HbA1c value of 8.0 or higher) at the time of screening (ii).5)Patients who have or are suspected of having an active infection at the time of informed consent (ii).6)Patients who test positive for HBs antigen, and HBs, HBc, and/or HCV antibodies (patients with positive HBs antibody and/or HBc antibody can be enrolled only when the HBV-DNA test is negative by taking appropriate measures, such as periodic monitoring of HBV-DNA and AST/ALT with reference to the Guidelines for Countermeasures Against the Onset of Hepatitis B; patients with positive HCV antibody can be enrolled only when the HCV-RNA test is negative), or patients with positive HIV or HTLV-1 antibody at the time of screening (ii).7)Patients with leukopenia (less than 2,000/mm^3^), neutropenia (less than 1,000/mm^3^), or lymphopenia (less than 500/mm^3^) at the time of screening (ii).8)Patients with an history of serious hypersensitivity or anaphylactic reaction to one of the ingredients in the investigational drug or murine protein-containing products.9)Patients who are judged to be having life-threatening nephrotic syndrome by the investigator or a sub-investigator at the time of informed consent (ii).10)Patients with serious comorbidity at the time of informed consent (ii).11)Female patients who are pregnant, lactating, or potentially pregnant, with obtainment of informed consent (ii), or who are unwilling to use contraceptive measures during the study period.12)Patients who are judged to be unsuitable by the investigator or a sub-investigator.

### Registration and randomisation

The investigators obtained written informed consent from all eligible patients, who were willing to enroll in the study. After all inclusion and exclusion criteria were confirmed, the investigators registered all items required for enrollment/eligibility confirmation on the electronic data capture system. Patients confirmed to eligible were randomly assigned to the rituximab or placebo group at a ratio of 1:1 in the minimization method according to the following factors: their urine protein/creatinine ratio (<5.0 g/g creatinine/≥5.0 g/g creatinine) at the time of the screening, and use of angiotensin converting enzyme inhibitor or angiotensin receptor blocker at the obtainment of consent (yes/no).

The investigators obtained written informed consent from all eligible patients who showed ICR II or NR until the time of evaluation at week 26 in the double-blind phase, met the re-administration criteria, and wished to have a re-challenge with rituximab. Subsequently, the patients were then registered on the electronic data capture system.

### Intervention and follow-up

Two randomized parallel-group controlled studies were performed on patients with membranous nephropathy with nephrotic syndrome as follows: one of these studies administered 375 mg/m^2^ rituximab intravenous infusion every week for two doses (days 1 and 8) [7], and the other study administered 1,000 mg of rituximab intravenous infusion every 2 weeks for two doses (days 1 and 15) [8,9]. In reference to these clinical studies, the KDIGO guidelines state the dosage and administration of rituximab as 1,000 mg intravenously every 2 weeks for two doses or 375 mg/m^2^ intravenously 1–4 times a week [4]. The dosages and administrations within these ranges may also be effective for Japanese patients with membranous nephropathy and nephrotic syndrome. Therefore, in the double-blind phase, an intravenous infusion of rituximab 1,000 mg or placebo was administered every 2 weeks for two doses. In the open-label phase, an infusion of rituximab (1,000 mg) was administered every 2 weeks for two doses.

All participants were followed-up for 26 weeks in the double-blind and open-label phases after the first dose of the investigational drugs; the planned visits and data collection are presented in Table 2. All data were collected using an electronic data-capture system and checked according to the data management and monitoring plan documented by each manager.

**Table 2 pone.0320070.t002:** Protocol for data collection from each patient enrolled in the double-blind and open-label phases of the PRIME study.

Visit	Screening	Start of dosing (Day 1)	Week 2 (Day 15)	Week 4 (Day 29)	Week 8 (Day 57)	Week 16 (Day 113)	Week 26 (Day 183)	At discontinuation
Visit + acceptable range (days)	-28 to -7	0	±3	±3	±7	±14	±14	+14
Dosing of investigational drug		X	X					
Patient background	X							
Serum or plasma pregnancy test	X^a^							
Vital signs^b^	X	X^c^	X^c^	X	X	X	X	X
Oxygen saturation	X	X^c^	X^c^	X				X
12-lead ECG	X							
Laboratory test (blood)^d^	X^e^	X	X	X	X	X	X	X
Laboratory test (random urine)^f^	X	X	X	X	X	X	X	X
Chest X-ray	X						X	X
Blood B cell^g^		X	X	X		X	X	X
Human anti-chimeric antibodies^g^		X				X	X	X
Blood drug level^g^		X^h^	X^h^	X	X	X	X	X
Concomitant drug/therapy	X	X	X	X	X	X	X	X
Adverse events		X	X	X	X	X	X	X

^a^Performed only in women with childbearing potential (women with childbearing potential are those meeting none of the following conditions: 1) had their last menstrual period at least one year ago, 2) underwent hysterectomy, and 3) underwent bilateral oophorectomy).

^b^Systolic and diastolic blood pressure, pulse rate, and body temperature.

^c^Measured within 30 min before starting the study drug administration, immediately before changing the infusion rate, at discontinuation/deceleration of administration, before resuming administration, within 10 min of the end of administration and an hour after the end of administration.

^d^Red blood cell count, white blood cell count, white blood cell differential count (neutrophil, lymphocyte, eosinophil, basophil, monocyte), platelet, haemoglobin, haematocrit, total protein, serum albumin, total bilirubin, direct bilirubin, aspartate amino transferase, alanine amino transferase, gamma-glutamyl transpeptidase, alkaline phosphatase, triglycerides, low-density lipoprotein cholesterol, choline esterase, uric acid, blood urea nitrogen, serum creatinine, creatine kinase, eGFR based on CKD-EPIcr equations, C-reactive protein, blood glucose, and electrolytes (Na, K, Cl, Ca, P, and Mg).

^e^HbA1c and infection tests (HBs antigen, HBs antibodies [HBV-DNA quantification if positive], HBc antibodies [HBV-DNA quantification if positive], HCV antibodies [HCV-RNA quantification if positive], HIV antibodies, and HTLV-1) have been added.

^f^Urine protein, creatinine, glucose, occult blood, and pH

^g^The results will not be disclosed until all the analysis data are fixed.

^h^Blood was collected within 15 min before the start of dosing and 15 min after the end of dosing.

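### Table 2, footnote a: a year without periods exempts a woman from the only pregnancy test scheduled in each phase, whether or not menopause is the cause (minor safety wording)

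*Protocol article*

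**What the plan says.** Table 2 (Protocol article, Intervention and follow-up) is titled "Protocol for data collection from each patient enrolled in the double-blind and open-label phases of the PRIME study", so one schedule serves both phases. Its row "Serum or plasma pregnancy test" has a single mark, in the screening column, and that mark carries footnote a.

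Footnote a restricts the test to women of childbearing potential and defines the term: "women with childbearing potential are those meeting none of the following conditions: 1) had their last menstrual period at least one year ago", with hysterectomy as the second condition and bilateral oophorectomy as the third.

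Three other places bear on the point:

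- Inclusion criterion 5 sets the lower age limit at 15 years.
- Exclusion criterion 13 bars "Female patients who are pregnant, lactating, or potentially pregnant, or patients who are not willing to use contraceptive measures during the study period". Exclusion 11 for re-administration is the counterpart at the second consent.
- Exclusion criterion 14 lets the investigator exclude anyone judged unsuitable. Exclusion 12 for re-administration does the same.

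**The concern.** Hysterectomy and bilateral oophorectomy end fertility for good. A year without periods does so only if menopause is the reason. Amenorrhoea of that length can also follow illness or earlier drug treatment in a premenopausal woman, who may still conceive. The footnote reads as a complete definition, and nothing else in the article adds an age, a cause or a menopausal status to its first condition.

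At stake is the objective exclusion of pregnancy before a B-cell-depleting antibody is given. The exempted women are also those for whom a missed period gives no warning, so the test is worth more in them than in women with regular cycles. The rule applies twice: before randomised treatment and before open-label rituximab.

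**Working it through.** The article gives no figure to reproduce here. The check is a reading of the rule, followed by a rough estimate of how many women it could affect.

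**Reading the rule**

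1. A woman is tested only if she meets none of the three conditions, so meeting any one exempts her.
2. Condition 1 is met by a year without periods from any cause.
3. A premenopausal woman with a year of amenorrhoea therefore meets condition 1 and is not tested.
4. Table 2 has no pregnancy test on Day 1, at weeks 2 to 26 or at discontinuation, so no later scheduled test makes up for the missed one.
5. Table 2 covers both phases, so the same exemption applies at open-label screening.
6. The exclusion criteria bar pregnant women but schedule no test.

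**Inputs from the article**

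- Target 88 patients, randomised 1:1; 40 enrolled by 24 September 2024.
- First registration 24 June 2023; first dose 30 July 2023, a lag of 36 days.
- Primary assessment at week 26 (182 days).
- Planning rates for the primary response: 22% on placebo and 52% on rituximab.

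**Assumptions (not in the article)**

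- 5–20% of patients are women able to conceive.
- 5–10% of those have had a year of amenorrhoea from a cause other than menopause.
- 1–2% of such untested women are pregnant.
- Accrual was even from the first registration.

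**Untested women per patient screened**

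- Low: 0.05 × 0.05 = 0.0025
- High: 0.20 × 0.10 = 0.02

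**First screenings that could still change**

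- 88 − 40 = 48
- Untested: 48 × 0.0025 = 0.12 to 48 × 0.02 = 0.96

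**Open-label screenings that could still change**

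- 24 June 2023 to 24 September 2024 is 458 days.
- Already at week 26, counting from registration: 40 × (458 − 182)/458 = 24.1
- Already at week 26, adding the first patient's 36-day lag: 40 × (458 − 218)/458 = 21.0
- Still to come: 88 − 24 = 64 to 88 − 21 = 67
- Eligible by response, as an upper bound: (44 × 0.78 + 44 × 0.48)/88 = 55.4/88 = 0.63
- Open-label screenings: 64 × 0.63 = 40.3 to 67 × 0.63 = 42.2
- Untested: 40.3 × 0.0025 = 0.10 to 42.2 × 0.02 = 0.84

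Some women would be counted in both phases, so the two counts should not be added as if they were different people.

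**Rituximab-exposed pregnancies**

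Half of the randomised patients receive rituximab in the first phase, and all treated patients do in the second.

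- Low: 0.5 × 0.12 × 0.01 + 0.10 × 0.01 = 0.0016
- High: 0.5 × 0.96 × 0.02 + 0.84 × 0.02 = 0.026

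These figures lean high: they assume that every non-responder moves to open-label treatment, and they ignore contraception during the first phase.

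**The case against.** The strongest objection is that this is a condensed footnote in a journal article. A full definition of childbearing potential normally sits in the full protocol, which is not shown. Next to two permanent surgical conditions, a year without periods reads naturally as shorthand for menopause, and trial physicians would probably take it so.

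The risk is also covered elsewhere. The exclusions for pregnant or potentially pregnant women and for those unwilling to use contraception do not depend on the footnote. Investigator judgement adds a further layer, and nothing forbids an unscheduled test. The Introduction calls membranous nephropathy "one of the most frequent causative diseases of nephrotic syndrome developing in middle-aged or older individuals", so few patients will be premenopausal. The estimate multiplies three assumed rates, and even its upper end is about one event in 38 such trials (1/0.026).

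Most of this stands, but it bears on the size of the problem. The footnote does not leave the definition to another document. It prints a closed rule, and that rule as printed is too broad. The exclusions tell the investigator to keep pregnant women out but do not restore the test for the exempted group. The estimate shows only an order of magnitude, and it supports a minor rating.

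**Conclusion.** The point holds as a minor fault of safety wording. As printed, footnote a withholds the only pregnancy test scheduled in each phase from some women who could still conceive. Their loss is that one check; the exclusions, the contraception requirement and investigator judgement remain.

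The expected numbers are very small: at most about one untested woman among the remaining first screenings, fewer than one at open-label screening, and a few hundredths of a rituximab-exposed pregnancy at the upper end. They rest on assumed rates of fertility, amenorrhoea and pregnancy, and on even accrual. Confidence is medium, because the full protocol may already carry the missing qualifier. Endpoints, power and analysis are not affected.

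**What to change.** Reword condition 1 of footnote a as: *postmenopausal (no menses for at least one year without another medical or drug cause)*. Give the screening test already scheduled, in both phases, to every other woman who is not surgically sterile.

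Check the full protocol first. If it already has this qualifier, correct only the article's footnote. If not, the cost is a routine blood test in a few more women and a minor amendment at the 15 sites, possibly with an update to the clinical trial notification. That is best bundled with the next amendment. Sample size, blinding and analysis stay as they are.
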